### Data Collection

The SCAT-5 form will be filled out at the time of biomarker analysis and used as a secondary endpoint of the study. The boxing bouts take place either in events consisting of single bouts for each boxer or in tournaments where 2 bouts are possible (semifinal and final). For boxers participating in two bouts at the same event, the baseline, postfight, and 45-minute postfight scores and biomarker tests will be retaken. Values related to the second fight will be considered in the analysis. The analysis of symptom severity scores obtained by SCAT-5 at the set timeline will facilitate the interpretation of outcomes between the boxers independent of their previous boxing history after the completed 6-day follow-up. Boxing history will be obtained by phone call interview at the 6-day follow-up or on-site. The follow-up for days 3 and 6 will be organized by the local clubs before the first postmatch training session, or at the study hospital.

### Sample Size and Statistical Power

Based on previous reports, an approximately 10% increase in key biomarkers is observed after a concussion in athletes [16]. We hypothesized a 20% reduction of biomarker level by acute head-and-neck cooling. We assumed equal variance of the cooled and control groups. The selected power was set to 0.8. Power analysis was conducted using the following formula:

[figure not shown]

[24]

Based on the power calculations, a total number of 20 participants per group is expected to yield sufficient statistical power. Since dropouts and missed sample times can be anticipated we aim for group sizes of 25 per group.

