**Results:**

Recruitment started in November 2021 and is ongoing. So far, 41 boxers have been included: 20 controls and 21 cooled. Data collection started in October 2024 following the completion of blood sample analysis. We expect to recruit more boxers before the middle of 2025, but challenges with recruitment may limit this.

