#### Trial Design

The head-and-neck Cooling of Brain temperature In BOXing (COBIBOX) trial is designed as a randomized, controlled, open, single-center superiority trial with 2 parallel groups and a primary endpoint of biomarker changes during the first 6 postfight days. Clinical secondary outcome assessments of a number of symptoms (NOS) and symptom severity score (SSS) using the symptom rating part of the SCAT-5 is performed during the initial 6 postinjury days. Randomization will be performed in blocks with 1:1 allocation.

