## Results

The study flow is presented in Figures 1 and 2. The study began in November 2021 and is expected to be completed before the summer of 2025 (Figure 4). Based on our sample size calculations, we aim to recruit approximately 40-50 participants. The first results are anticipated to be submitted for publication in the Autumn of 2025. This study evaluates the effectiveness of selective head and neck cooling in reducing blood-brain biomarkers and SCAT-5 scores during the first week after a boxing bout. Recruitment started on November 4, 2021. Approximate completion of final recruitment is expected in the first weeks of January 2025 (protocol version 1.0, 2024-04-01).

The 3 excluded boxers, whose opponents dropped out, went through baseline SCAT-5 testing and blood sample collection. The participant who experienced nausea and vomiting chose to withdraw from participation in the study after his boxing bout before any further testing (Figure 4).

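### The recruitment aim of about 40-50 attributed to the sample size calculation drops, at its lower end, the allowance for loss that took the target from 20 to 25 per group

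*Protocol article*

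**What the plan says.** Under Sample Size and Statistical Power, the protocol article fixes the power, "The selected power was set to 0.8", and gives the number that is meant to deliver it: "a total number of 20 participants per group is expected to yield sufficient statistical power". The next sentence gives a reason for raising that number, "Since dropouts and missed sample times can be anticipated", and then the raised number: "we aim for group sizes of 25 per group". With the 1:1 allocation stated under Trial Design, this is 50 boxers.

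The main Results section gives the aim again, as a range: "Based on our sample size calculations, we aim to recruit approximately 40-50 participants". It also mentions three boxers excluded because their opponents dropped out, and one who withdrew after his bout before further testing.

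The Results paragraph of the abstract reports progress: "So far, 41 boxers have been included: 20 controls and 21 cooled". It adds that more boxers are expected by mid-2025, although recruitment difficulties may limit this.

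The abstract's Methods paragraph defines the primary endpoint as the change in biomarkers from immediately after the fight to day 6. A boxer without a day 6 sample therefore does not contribute a complete primary observation.

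**The concern.** One calculation cannot both require a margin for loss and support an aim that has none. The sample size section treats 20 per group as the number needed for analysis and 25 per group as the number to recruit. The Results section puts the two into one range and presents the whole range as following from the calculation.

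At stake is how a finished trial would be described. If recruitment closed at 40 or 41, the trial could be said to have met its aim, and a reader would assume a power of 0.8. If boxers were then missing at day 6, as the plan itself anticipates, power for the planned difference would be below 0.8. A null result would be taken as stronger evidence against an effect than it is.

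**Working it through.** **Inputs from the protocol article.** Power 0.8; 20 per group sufficient; 25 per group recruited; 1:1 allocation; recruitment aim 40-50; 41 included (20 control, 21 cooled); four boxers reported as excluded or withdrawn.

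**Inputs not readable.** The formula is a figure that is not shown, and the readable text gives no alpha, sidedness or SD. The 20 per group therefore cannot be rebuilt independently and is taken as given. I assume a two-sided 5% two-sample t-test and vary this below.

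**Step 1: the plan's own inflation.** No loss rate is stated. The implied rate is 1 - 20/25 = 0.20, and 20/(1 - 0.20) = 25. The step from 20 to 25 is consistent in itself.

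**Step 2: the range.** 2 x 20 = 40 and 2 x 25 = 50. The lower end is the number before inflation and the upper end the number after it.

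**Step 3: the standardised difference implied by the plan.** Power is the probability that a noncentral t variable with n1 + n2 - 2 degrees of freedom and noncentrality d / sqrt(1/n1 + 1/n2) exceeds the two-sided 5% critical value. Setting power to 0.80 at n1 = n2 = 20 gives d = 0.909. The normal approximation gives d = sqrt(2/20) x (1.960 + 0.842) = 0.886.

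**Step 4: power for that d at the numbers in question.**

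| Recruited | Loss | Evaluable | Power (t-test) |
|---|---|---|---|
| 50 | none | 25 + 25 | 0.883 |
| 50 | 20% | 20 + 20 | 0.800 |
| 40 | none | 20 + 20 | 0.800 |
| 40 | 10% | 18 + 18 | 0.755 |
| 40 | 20% | 16 + 16 | 0.701 |
| 41 | none | 20 + 21 | 0.810 |
| 41 | 4 boxers | 18 + 19 | 0.767 |
| 41 | 20% | 16 + 17 | 0.715 |

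The normal approximation gives 0.757 at 18 per group and 0.707 at 16 per group. The row with four boxers lost assumes two from each group, since the text does not give their allocation.

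**Step 5: sensitivity to the missing alpha.** Solving again for d under other assumptions, power at 16 per group is 0.715 with a one-sided 5% test (d = 0.801) and 0.672 with a two-sided 1% test (d = 1.130). Across these variants and both formulas the range is 0.67 to 0.72. It is narrow because d is always anchored to the plan's own statement that 20 per group gives 0.8.

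**Step 6: detectable difference.** At fixed power this grows approximately as sqrt(20/n): sqrt(20/18) = 1.05 and sqrt(20/16) = 1.12. With 16 per group evaluable, 0.8 power would apply to a difference about 12% larger than planned.

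**The case against.** The strongest reply is that nothing has been miscalculated. The governing target is in the sample size section. The Results sentence is an approximate progress statement, and its range includes 50. The 20% loss is never stated, and going from 20 to 25 may simply be a round margin. This stands in part: the fault is an inconsistency between two statements of the target, and any single power figure below 0.8 is conditional on a loss rate. The inconsistency remains, because the Results section explicitly derives its range from the calculation.

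Three stronger readings are tempting, and the documents do not support them.

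- A reader might infer that the lower end simply has about 70% power. That needs the implied 20% loss. With 10% loss the figure is 0.755, and with no loss it is 0.80.
- A reader might infer that the trial is already short at 41. Whether the 41 are counted before or after the three exclusions and the withdrawal cannot be told from the text, since the flow is in Figure 4, which is not shown. If the 41 are net of those four, the known loss is 4/45 = 9%, and 41 stand against the 40 needed, with power 0.81 if all have day 6 samples. Day 6 completeness is not reported either way.
- A reader might infer that recruitment has all but stopped. The abstract says that more boxers are expected and that difficulties may limit this. It discloses a risk and does not predict closure at 41.

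**Conclusion.** The point holds as a conflict between two stated recruitment aims: 50 in the sample size section, and about 40-50 in the Results section on the strength of the same calculation. Only the top of the range keeps the plan's full allowance for loss.

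The possible loss of power ranges from nothing to about 10 percentage points at 40 recruited (0.80 down to 0.70). At the 41 already included it runs from 0.81 down to about 0.715. These figures rest on three assumptions: that 20 per group does give 0.8, that the test is a two-sided 5% t-test, and that loss is no more than the 20% implied by the inflation. They do not show whether 20 per group is itself the right number, which cannot be checked without the SD and alpha. The conflict in the target does not depend on any of them.

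**What to change.** In the Results section, replace the 40-50 range with the single target from the sample size section: 50 boxers randomised, 25 per group. Say there that 20 per group evaluable at day 6 is the number that carries the power of 0.8.

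If recruitment closes with fewer than 20 per group evaluable at day 6, restate the power and the detectable difference at the number actually evaluable, using the trial's own alpha and SD, and do not carry 0.8 forward. The power figures above should not be copied into the protocol, because they rest on an assumed alpha and loss rate.

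The cost is a change of wording and possibly a less favourable stated power. The target of 50 is already in the plan, so no extra boxers are required.

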### Recruitment

Participants are recruited by one researcher ([name]) by sending information about the study to the Swedish Boxing Association which approves participation, in written form or verbally. Thereafter the study must be approved by the organizers of the boxing tournament. Finally, the recruitment of boxers who fulfill the inclusion criteria and sign the written consent form after verbal and written information about the study is provided.

### Adverse Events

Any adverse events reported by the participant during the study period are noted and reported. Specifically, any deviation from the protocol (eg, sample time point, duration of head-and-neck cooling) will be noted. Symptoms, such as headache, nausea, and dizziness, are reported to the medical doctor and study researcher ([name]), although these symptoms may also be caused by the SRC per se [15]. No adverse events are expected, based on our previous study where 61 elite ice hockey players were cooled without any reported adverse events [15].

## Results

The study flow is presented in Figures 1 and 2. The study began in November 2021 and is expected to be completed before the summer of 2025 (Figure 4). Based on our sample size calculations, we aim to recruit approximately 40-50 participants. The first results are anticipated to be submitted for publication in the Autumn of 2025. This study evaluates the effectiveness of selective head and neck cooling in reducing blood-brain biomarkers and SCAT-5 scores during the first week after a boxing bout. Recruitment started on November 4, 2021. Approximate completion of final recruitment is expected in the first weeks of January 2025 (protocol version 1.0, 2024-04-01).

The 3 excluded boxers, whose opponents dropped out, went through baseline SCAT-5 testing and blood sample collection. The participant who experienced nausea and vomiting chose to withdraw from participation in the study after his boxing bout before any further testing (Figure 4).

**Figure 4 figure4:**
[figure not shown]
All allocation and randomization occur after signed informed consent and before baseline testing.

## Discussion

### Principal Findings

During a boxing fight, boxers typically attain a high number of blows to the head, which may lead to brain injuries. Due to the strenuous activity, these blows occur at a time of elevated core body temperature, which may exacerbate the brain injury. There are no approved treatments for boxing-induced brain injuries. A blow to the head may lead to an elevation of blood biomarker concentrations that reflect the degree of the brain injury caused by the impact. There is an increasing interest in these biomarkers that include markers for large caliber axon injury (NFL), neuronal injury (NSE, tau), and glial injury (S100B, GFAP). Our present study may show whether the level of biomarkers is related to the number of hits or concussions received, the symptom development after the fight, and most importantly the effects of the cooling intervention.

Head-and-neck cooling was shown to decrease brain temperature measured by magnetic resonance imaging (MRI) [25], and improved cognitive outcome when applied acutely post concussion [26]. In a recent clinical trial including 132 concussed ice hockey players, a shorter recovery time was observed after acute selective head-and-neck cooling for at least 45 minutes [15]. A shorter recovery was also observed when cooling was initiated up to 8 days post concussion [27]. To provide an objective outcome measure for the cooling intervention in the present study, the primary outcome is blood biomarker levels, of which GFAP, NFL, S100B, and tau may be the most important. The chosen time points for collecting blood-brain biomarkers aim to assess the early-phase biomarker response to boxing matches, with subsequent evaluation of the head and neck cooling effect and its potential early impact. S100B is associated with an acute astrocytic response, which typically peaks within hours, followed by GFAP with a peak of 24 hours [28]. This makes postfight day 3 a valuable time point to capture a delayed peak or sustained elevation of the selected biomarkers. While NFL levels may remain elevated at longer time points post fight, we had to use 6 days as our latest evaluation time point. This is based on the guidelines of the Swedish Boxing Association, which prohibit boxers from competing or having fights within 6 days of their most recent tournament. Thus, many boxers are assigned to match sparring or other tournaments after 6 days.

The selection of biomarkers in the present trial is based on several previous studies [29,30], mainly in traumatic brain injury and neurodegenerative disorders [19]. Currently, both tau isoforms and GFAP are used in the prediction and diagnosis of neurodegenerative diseases, particularly Alzheimer disease, and S100B in mild traumatic brain injury guidelines [31-33].

In numerous reports on mild, moderate, or severe traumatic brain injury, blood and CSF biomarkers have been used at different time points postinjury [29]. Following boxing bouts, tau, NFL, GFAP, and S100B are all increased in the early phase after boxing. Of these, NFL, GAP, and tau are increased several weeks to months post fight [16,17,34].

In addition, strenuous exercise has been reported to increase biomarkers such as S100B [35,36]), while leading to a reduction in GFAP and no alteration in NF-L levels [37]. When comparing strenuous exercise to contact sports such as boxing, boxers showed a significant increase in biomarker levels, particularly in GFAP and NFL [17].

Blood S100B levels were significantly elevated in both competitive boxers and high-level exercised athletes such as runners [16,38]. These findings argue that boxing causes the elevation of concentration of several biomarkers reflecting the brain injury, and is associated with lead to long-term neurological consequences.

The role of brain temperature in acute brain injury has been evaluated in numerous trials. In particular, elevated brain temperature may negatively impact functional and neurological outcomes following traumatic brain injury [39,40]. While systemic hypothermia has not been associated with improved outcomes in severe traumatic brain injury, we hypothesized that controlling body temperature may be an important factor in the recovery of boxing-induced brain injury. The primary aim of head-and-neck cooling is not to provide cerebral hypothermia, it is to attenuate exercise-induced hyperthermia and to rapidly normalize the elevated brain temperature.

During exercise, elevated temperature is associated with a higher demand for oxygen and energy metabolism in the brain [41,42], resulting in exacerbation of the injury mechanism initiated by head impacts during boxing. We hypothesize that brain cooling can rapidly normalize brain temperature, thereby reducing metabolic demand resulting in attenuated secondary injury and leading to beneficial effects for the recovery phase after a fight.

Should this explorative study provide evidence of the beneficial effects of head-neck cooling, a multicenter study (preferably with later postfight time points) is warranted.

### Strengths and Limitations

The present study has the potential to objectively evaluate the effect of head-and-neck cooling on blood biomarker levels. Moreover, it can provide unique results on biomarker concentration changes following repeated head impacts at several time points post fight.

Outliers in biomarker concentrations are expected, although since each boxer will be his or her control, percentage changes from baseline can be calculated. A 20% reduction of biomarker concentrations is reasonable based on the rapid application of head-and-neck cooling. The potential placebo effect of cooling on symptom ratings is also taken into consideration by using objective biomarker concentrations, highlighting the necessity of biomarker assessment to evaluate cooling’s physiological impact.

### Conclusion

This study is structured to evaluate early-phase objective and subjective changes in boxers during the first week post fight, and to study the effects of head-and-neck cooling on these changes. In conclusion, the present trial may provide objective biomarker evidence for the role of attenuating cerebral hyperthermia by selective head-and-neck cooling acutely following a boxing bout.

## Data Availability

The datasets generated or analyzed during this study are available from the corresponding author on reasonable request.

## Appendix

Multimedia Appendix 1 SPIRIT (Standard Protocol Items: Recommendations for Interventional Trials) checklist COBIBOX.

## Abbreviations

COBIBOX: Cooling of Brain temperature In BOXing
CTE: chronic traumatic encephalopathy
GFAP: glial fibrillary acid protein
MRI: magnetic resonance imaging
MMA: mixed martial arts
NSE: neuron specific enolase
NFL: Neurofilament light
NOS: number of symptoms
RHI: repetitive head impacts
S100B: S100 calcium-binding protein
SCAT-5: Sports Concussion Assessment Tool-5
SRC: sport-related concussion
SBA: Swedish Boxing Association
SPIRIT: Standard Protocol Items: Recommendations for Interventional Trials
SSS: symptom severity score
Tau: tubulin-associated unit
